## Abstract

**Background:**

Human milk is recommended for very preterm infants, but its variable macronutrient content may contribute to undernutrition during a critical period in development. We hypothesize that individually targeted human milk fortification is more effective in meeting macronutrient requirements than the current standard of care.

**Methods:**

We designed a single-center randomized, controlled trial enrolling 130 infants born < 31 completed weeks’ gestation. Participants will receive fortified maternal and/or pasteurized donor milk but no formula. For participants in the intervention group, milk will be individually fortified with protein and fat modulars to achieve target levels based on daily point-of-care milk analysis with mid-infrared spectroscopy, in addition to standard fortification. The study diet will continue through 36 weeks’ postmenstrual age (PMA). Clinical staff and parents will be masked to study group. Primary outcomes include: 1) body length and lean body mass by air displacement plethysmography at 36 weeks’ PMA; 2) quantitative magnetic resonance imaging-based measures of brain size and microstructure at term equivalent age; and 3) Bayley-IV scales at 2 years’ corrected age.

**Discussion:**

We expect this trial to provide important data regarding the effectiveness of individually targeted human milk fortification in the neonatal intensive care unit (NICU).

**Trial registration:**

NCT03977259, registered 6 June, 2019.

## Background

For hospitalized very preterm infants, the two to 4 month-long neonatal intensive care unit (NICU) hospitalization coincides with a critical period in development during which the brain is uniquely sensitive to nutrition [1, 2]. The use of human milk is recommended based on strong evidence of short- and long-term benefits [3, 4]. Aiming to support fetal rates of physical growth and tissue accretion [5–7], multi-component human milk fortification is recommended [8, 9] and practiced widely [10]. However, epidemiologic data indicate that NICU growth outcomes remain far short of the goal to match in-utero growth [11, 12]. Additionally, we and others have reported slower weight gain and head circumference growth among fortified human milk-fed as compared with preterm formula-fed infants [13–17], suggesting gaps in current fortification strategies. These gaps are particularly relevant given the recent rise in the use of both maternal and donor milk NICUs [18].

A major challenge in clinical care is that in prescribing nutritional interventions, NICU clinicians rely on published average nutrient values [5, 9] whereas the actual macronutrient content of human milk varies considerably [19]. Pasteurized donor milk is also variable and is, on average, lower in protein content than maternal milk [20, 21]. Thus, over time, and despite standard fortification, some preterm infants may accumulate protein and/or energy deficits that adversely impact their physical growth and/or brain development, with likely implications for long-term neurodevelopmental outcomes.

The recent availability of a reliable point-of-care human milk analyzer provides an opportunity to individually target fortification of human milk in the NICU. However, only a few randomized trials have examined the effectiveness of this approach in improving physical growth [22], and the results have been inconsistent. Additionally, virtually no data exist on outcomes beyond NICU discharge, and effects of an individualized approach to human milk fortification on structural brain development during the neonatal period are unknown.

To address these knowledge gaps, we designed Nourish as a single-center randomized, controlled clinical trial designed with the aim of evaluating the effectiveness of individually targeted human milk fortification, as compared with standard-of-care fortification, in promoting physical growth, structural brain development, and neurodevelopmental outcomes in very preterm infants. Primary outcome domains for Nourish are: 1) physical growth during the intervention; 2) magnetic resonance imaging (MRI) based measures of brain development at term equivalent age; and 3) neurodevelopmental outcomes at 2 years’ corrected age. The overall hypothesis is that minimizing protein and energy deficits by individually targeting human milk fortification during the NICU hospitalization will improve physical growth, regional brain development, and neurodevelopmental function.

## Methods / design

### Setting and eligibility criteria

This randomized clinical trial will take place at Brigham and Women’s Hospital, an academic Level III NICU in Boston, MA. Inclusion criteria are: 1) singleton or twin infant with gestational age at birth 24 0/7 to 30 6/7 weeks; 2) chronologic age < 21 days; and 3) mother providing milk, with clinical consent given to use pasteurized donor human milk if maternal milk is in short supply or unavailable. Exclusion criteria include: 1) major congenital anomaly; 2) birth weight < 3rd percentile [23]; 3) necrotizing enterocolitis or other clinically significant gastrointestinal pathology; 4) clinically significant renal or hepatic dysfunction or inborn error of metabolism; 5) fluid restriction < 140 mL/kg/day anticipated for 3 or more days; 6) grade 3 or 4 intraventricular hemorrhage detected prior to enrollment; and 7) anticipated transfer < 36 weeks’ postmenstrual age or expected death.

### Informed consent

Written, informed consent from one parent will be obtained by a research nurse, dietitian, or physician. Consent documents will be available in English and Spanish and will cover both clinical trial participation and the use of data and/or bio-specimens for future research. Separate consent forms will be used for the NICU and follow-up phases. This study protocol (2019P000893) was approved by the Partners Human Research Committee (FWA00000484) on June 25, 2019.

### Milk collection, pooling, and analysis

As soon as possible after delivery, mothers of all preterm infants admitted to the NICU receive standard written and verbal instructions by a board-certified lactation consultant to express milk at least 8 times per day with a double-electric breast pump, augmented with hand expression to improve emptying. For enrolled infants during the study diet period, each weekday, research assistants will pool fresh maternal milk and supplement with frozen maternal milk and/or donor milk as needed based on the daily volume ordered by the clinical team (typically 150–160 mL/kg/day). From these 24-h pools, 3 mL of milk will be sonicated for 5 s and warmed to 40 °C using a bead warmer, then analyzed for macronutrient content with a mid-infrared spectroscopy-based human milk analyzer (sonicator, bead warmer, and analyzer all Miris AB, Uppsala, Sweden) [24]. Each sample of milk will be analyzed once.

### Intervention

The study period will start the first weekday that the infant reaches the clinical standard goal human milk diet, defined as ≥140 mL/kg/day fortified with multicomponent liquid human milk fortifier (Similac human milk fortifier hydrolyzed protein concentrated liquid, Abbott Laboratories, 5 mL added to 25 mL milk, equivalent to 24 kcal/ounce assuming the ‘base’ milk is 20 kcal/oz) plus liquid protein fortifier (Abbott Laboratories) at 0.27 g/dL (“Step 1” assuming that the ‘base’ milk contains 1 g/dL protein, with the goal to provide ≥4 g/kg/day protein) and is not receiving IV fluids. Throughout the trial, if maternal milk is in short supply or not available, pasteurized donor human milk (“donor milk”) will be used. To reduce variability of donor milk macronutrient composition, particularly of protein which declines with advancing lactation duration [21], we will use pasteurized milk that was expressed within 3 months of delivery, provided by a community-based milk bank affiliated with the Human Milk Banking Association of North America (Mother’s Milk Bank Northeast, Newton MA). Infant formula will not be used for supplementation during the study period. Routine electrolyte monitoring and supplementation and supplementation of Vitamin D and iron for all participants will follow a local Enteral Nutrition Clinical Guideline, available upon request.

In addition to the standard-of-care diet of human milk (maternal and/or donor) with multi-component HMF to 24 kcal/oz. and “Step 1” protein, milk for infants in the intervention group will be additionally fortified with liquid protein (Abbott Laboratories) and/or medium chain triglyceride (MCT) oil (Dot Foods, Nestle USA) to ensure target levels in the ‘base’ milk of 1 g/dL for protein and 3.9 g/dL for fat (Fig. 1). Individual recipes are calculated in a custom-built Excel spreadsheet based on data input including the infant’s body weight, daily fluid volume, and milk macronutrients. Currently, we do not have access to a sterile carbohydrate modular, which means that even after target levels of protein and fat are reached, the energy content may remain below the target of 67.7 kcal/dL. Should energy content fall below this target, we will add more MCT oil to achieve the energy target. We will use the following formula to calculate the energy content of milk: 9*fat + 4*protein + 4*carbohydrate [25] with fat, protein, and carbohydrate values taken from the milk analysis. We will use the “true protein” value (crude protein*0.8) to account for non-protein nitrogen [24].

**Fig. 1 Fig1:**
[figure not shown]
Schematic of standard fortification and individually targeted fortification in the Nourish study. Standard fortification will be provided for all participants and comprises 1) multicomponent liquid human milk fortifier (Similac human milk fortifier hydrolyzed protein concentrated liquid, Abbott Laboratories), 5 mL added to 25 mL milk and 2) liquid protein fortifier (Abbott Laboratories) at 0.27 g/dL. Milk for infants in the intervention group will also be individually fortified with liquid protein (Abbott Laboratories) and/or medium chain triglyceride (MCT) oil (Dot Foods, Nestle USA) to ensure target levels in the ‘base’ milk of 1 g/dL for protein, 3.9 g/dL for fat, and 67.7 kcal/dL for energy. If maternal milk is in short supply, pasteurized donor milk expressed within 3 months of delivery will be used. The study diet will continue through 36 weeks’ postmenstrual age

### Management of growth faltering

Growth faltering is defined as an average weight gain < 15 g/kg/day or gain in body length < 0.8 cm per week. Management of growth faltering among participants will proceed as follows: 1) increase enteral feeding volume by 10 mL/kg/day, if acceptable to the clinical team; 2) add MCT oil to increase energy density to 26 kcal/oz. based on assumed ‘base’ milk energy content of 20 kcal/oz.; 3) increase standard liquid protein fortifier to 0.54 g/dL (“Step 2”); and 4) further increase standard energy density to 28 kcal/oz. with MCT oil and/or increase protein to 0.8 g/dL (“Step 3”).

### Criteria for discontinuing or modifying allocated interventions

If growth faltering persists despite taking the above steps, partial formula supplementation will be considered by the clinical and research teams. Participants will be removed from the study if they develop NEC or any other exclusion criteria, or at parent request.

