### Blinding

Parents, clinical staff, and all study staff apart from the research assistants who prepare the study diet will be blinded to the study group. Blinding will be facilitated by the use of amber enteral feeding tubes to hide the appearance of the milk. Unblinding will be permitted if an error in milk preparation is identified, if a participant experiences growth faltering despite all strategies outlined in the protocol, or if unexpected safety concerns arise that require unblinding.

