### Statistical methods

Our overall analytic strategy compares pre-specified primary and secondary outcomes between control and intervention groups. We will follow the intention-to-treat principle and analyze data for all enrolled participants. We will use multiple imputation to address missing data due to death or loss to follow-up. Results will be expressed as mean or median differences with 95% confidence intervals. We will use mixed linear models adjusted for intrafamilial clustering due to multiple births, along with control for baseline covariates, as needed, to minimize effects of between-group differences in baseline factors due to chance. We will examine intervention effects in the complete cohort and use stratification approaches to explore the effects of variables specified a priori including sex, fetal growth status (SGA vs. non-SGA), and gestational age (24–27 weeks vs. 28–30 weeks).

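### The protocol rules out formula during the study period but also allows it for persistent growth faltering, at a point where unblinding is permitted too

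*Protocol article*

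**What the plan says.** All references are to the protocol article.

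- Abstract, Methods: "Participants will receive fortified maternal and/or pasteurized donor milk but no formula".
- Intervention: "Infant formula will not be used for supplementation during the study period". The sentence has no exception and no cross-reference.
- Management of growth faltering, which gives the trigger: "Growth faltering is defined as an average weight gain < 15 g/kg/day or gain in body length < 0.8 cm per week". Four escalation steps follow. They apply to participants generally and use feed volume, MCT oil and liquid protein.
- Criteria for discontinuing or modifying allocated interventions, which opens the door to formula: "If growth faltering persists despite taking the above steps, partial formula supplementation will be considered by the clinical and research teams". This is not limited to one arm.
- Blinding: unblinding is permitted, among other reasons, "if a participant experiences growth faltering despite all strategies outlined in the protocol".
- Statistical methods: "We will follow the intention-to-treat principle and analyze data for all enrolled participants". Formula receipt is not mentioned.

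The Abstract names body length and lean body mass at 36 weeks' postmenstrual age as primary outcomes. The study diet runs to that same age, so any formula rescue during the diet comes before those measurements.

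**The concern.** For an infant who keeps faltering after the four steps, two sections say formula is not used and a third says it may be. The two answers describe different trials. One compares two human-milk-only diets. The other compares two strategies that start with human milk and permit formula.

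The second matters statistically because the trigger, weight or length gain, lies in the same domain as the growth outcomes. The Background hypothesises that the intervention "will improve physical growth, regional brain development, and neurodevelopmental function". If so, controls would falter more often and be considered for formula more often. The Background also reports "slower weight gain and head circumference growth among fortified human milk-fed as compared with preterm formula-fed infants", so on the protocol's own account formula can affect growth.

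The Blinding section adds a second problem. Persistent faltering after all listed strategies is both a ground for unblinding and, in effect, the trigger for considering formula. No order between the two is fixed, so the decision could be taken by people who know the arm.

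**Working it through.** **Step 1: the sections side by side, for one infant still faltering after the four steps.**

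| Section | Formula? | Arm known? |
|---|---|---|
| Abstract, Methods | No | not addressed |
| Intervention | No, for the study period | not addressed |
| Criteria for discontinuing or modifying | May be given in part | not stated |
| Blinding | not addressed | Unblinding permitted |

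Rows 1 and 2 cannot both hold with row 3. Rows 3 and 4 share a trigger, and their order is not stated.

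**Step 2: direction.** Let pC and pI be the shares of control and intervention infants given formula, and r the share of the between-arm deficit that formula makes up in an infant who receives it. With true difference D under a no-formula contrast, the intention-to-treat difference is

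D × [1 − r × (pC − pI)].

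This is below D whenever r > 0 and pC > pI. The hypothesis implies the second condition. The Background supports the first for weight and head circumference only.

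**Step 3: the plan's own figure.** Weight is used because it is a detectable difference in Sample size to which the Background evidence applies. Inputs from Sample size: 65 per group, 5% attrition, α = 0.05 (two-sided assumed), power 0.8, detectable difference 0.49 z-scores. No standard deviation is given. Clustering of twins is ignored here.

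Detectable difference = (1.960 + 0.842) × SD × √(2/n).

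- SD = 1, n = 65: 0.491.
- SD = 1, n = 65 × 0.95 = 61.75: 0.504.
- 0.49 at n = 61.75 requires SD = 0.49/0.504, about 0.97.

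The stated figure therefore cannot be reproduced exactly, but it fits an SD close to 1. SD = 0.97 is used below so that power starts at 0.80.

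**Step 4: illustration.** The rescue rates and r are assumptions; the documents give none.

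| pC − pI | Difference, r = 0.5 | Power | Difference, r = 1 | Power |
|---|---|---|---|---|
| 5 points | 0.478 | 0.78 | 0.4655 | 0.76 |
| 10 points | 0.4655 | 0.76 | 0.441 | 0.71 |
| 20 points | 0.441 | 0.71 | 0.392 | 0.61 |

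Example: 0.49 × (1 − 1 × 0.10) = 0.441.

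**Step 5: a check on plausible excesses.** Formula is open to both arms, so the excess is less than the control rate. If rescue follows a fixed cut-off on a normal growth distribution shifted by 0.49 (SD 0.97), control rates of 5%, 10%, 20% and 30% imply intervention rates of about 1.6%, 3.7%, 8.9% and 15.2%. The excesses are then 3.4, 6.3, 11.1 and 14.8 points. With r = 1, power is 0.77, 0.75, 0.70 and 0.67.

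**The case against.** The strongest reply is that there is no contradiction, only a default and an exception. The Intervention sentence follows text on short milk supply, the later section is headed as a modification of the allocated diet, and abstracts condense. This reading is reasonable. It does not rescue the text, because the Intervention sentence covers the whole study period, the Abstract describes the whole diet, and neither points to an exception. On this reading too, the human-milk-only description is wrong as written.

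Second, rescue is open to both arms and the analysis is by intention to treat, so the result is a valid comparison of strategies with permitted rescue. This stands. A reader might infer that the primary analysis is biased; the documents do not support that. The difference is smaller only relative to a no-formula contrast, which is the contrast the Abstract describes.

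Third, a reader might infer an established pull toward no difference in length, lean mass and brain volume. The Background evidence covers weight and head circumference, and compares formula-fed infants with infants fed fortified human milk. It does not address late, partial supplementation. Extending it to those outcomes is inference.

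Fourth, formula comes last. The four earlier steps also apply in both arms, some use the same kinds of product as the intervention, and they could narrow the contrast in the same direction. Formula is only part of the effect, and few infants may reach it.

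Fifth, the Blinding section does not say that unblinding comes before the formula decision. That is correct: the text leaves the possibility open and does not show that it will happen.

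Finally, how the analysis treats formula receipt in detail is commonly left to the statistical analysis plan, which is not at hand. Its absence is not part of this point.

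**Conclusion.** The point holds as an internal contradiction with two consequences. The stated human-milk-only contrast is not the one delivered if formula rescue is used. A discretionary co-intervention triggered by growth may be decided with the arm known. Neither depends on how many infants are affected.

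The effect on the growth comparison is conditional. It needs the intervention to work as hypothesised and formula to aid growth. Its size cannot be derived from the documents. For weight, with an assumed SD of 0.97 and assumed control excesses of 5 to 20 points, power falls from 0.80 to between 0.78 and 0.61. The low end requires a 20-point excess and full recovery of the deficit by partial formula, so it is a pessimistic bound and not an expectation.

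A reader might also picture different sites applying different rules. The trial has one center, so the inconsistency would arise between staff or over time at that center.

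**What to change.** 1. Reconcile the Abstract, Intervention and Criteria for discontinuing or modifying sections so that one rule on formula holds in both arms. Which rule is for the sponsor to decide.
2. If formula remains possible, describe the comparison in the Abstract and Intervention sections as human milk with permitted formula rescue.
3. In that case also reconcile the Criteria and Blinding sections by stating that the formula decision is taken masked to arm. This concerns who knows the allocation when the decision is made, not whether formula is given.
4. Report the number of infants receiving formula by arm alongside the intention-to-treat result. The analysis by randomised group is already committed to and needs no change.

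The cost is a few sentences of protocol text, one extra tabulation and a slightly less clean stated contrast. Sample size and primary analysis are unaffected.

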### Sample size

The planned sample size is 130 infants (65 per study group). Accounting for expected attrition (5% by NICU discharge due to death or unexpected transfer) and an additional 5% loss due to uncorrectable motion artifact for MRI outcomes, we expect to be able to detect a moderate effect of the intervention on primary outcomes (0.49 z-scores in weight, 0.24 z-scores in fat free mass, 24 cc total brain volume) at α = 0.05 and power 0.8. Accounting for 10% further attrition to 2 years’ corrected age, we have adequate power to detect an 8.1-point difference between groups on the Bayley cognitive scale.

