### Assignment of interventions

We will use permuted block randomization and assign participants 1:1 to the standard of care diet (control) or individually fortified diet (intervention). Twins will be randomized individually. The study biostatistician will generate the allocation sequence and place the assignments in envelopes, to be opened by the research assistants on the study start date.

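### Infants who develop NEC or another exclusion criterion after randomisation are to leave the study, which conflicts with the stated intention-to-treat analysis

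*Protocol article*

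**What the plan says.** Under the heading "Criteria for discontinuing or modifying allocated interventions", the protocol article states: "Participants will be removed from the study if they develop NEC or any other exclusion criteria, or at parent request".

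The exclusion list in Setting and eligibility criteria includes conditions that can newly arise while an infant is on the study diet:
- "necrotizing enterocolitis or other clinically significant gastrointestinal pathology; 4) clinically significant renal or hepatic dysfunction or inborn error of metabolism" (an inborn error of metabolism could only be newly recognised)
- "fluid restriction < 140 mL/kg/day anticipated for 3 or more days"
- anticipated transfer before 36 weeks' postmenstrual age, or expected death

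Two items on the list cannot become triggers later. Severe intraventricular haemorrhage counts only if found before enrolment, and birth weight is fixed at birth.

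Assignment of interventions says that the envelopes are "to be opened by the research assistants on the study start date". Statistical methods says "We will follow the intention-to-treat principle and analyze data for all enrolled participants" and "We will use multiple imputation to address missing data due to death or loss to follow-up". Sample size allows for a loss of "5% by NICU discharge due to death or unexpected transfer", a further 5% for MRI motion artefact, and 10% more by 2 years.

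**The concern.** The heading is about the intervention, but the rule under it takes the infant out of the study. The article nowhere says that such an infant still has the 36-week measurements, the MRI at 38–41 weeks or the 2-year Bayley. If staff follow the sentence as written, outcomes that could have been measured are not collected, and no later analysis can recover them.

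The triggers mark sicker infants, so the missing data would be related to prognosis. They occur after randomisation, under a diet that differs between arms in enteral protein and fat, so their frequency could differ by arm. All three primary outcome domains would be exposed. The imputation sentence names death and loss to follow-up; removal by protocol rule is neither. The attrition allowance does not name it either, except where it overlaps with death and transfer.

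**Working it through.** **1. Order of events.** Assignment is opened on the study start date and the diet runs to 36 weeks' postmenstrual age. An exclusion criterion that develops during the diet therefore develops after randomisation. Intention to treat requires that infant's outcome in the assigned arm; the removal sentence, read literally, ends its collection. The two statements cannot both be carried out.

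**2. The plan's own figure.** Sample size gives 8.1 Bayley points but no SD. I assume SD 15, two-sided α = 0.05 and power 0.80, with difference = SD × (1.960 + 0.842) × √(2/n per arm).
- Infants at 2 years: 130 × 0.95 × 0.90 = 111.2, or 55.6 per arm.
- Difference: 15 × 2.802 × √(2/55.6) = 7.97 points, or 8.04 with the t distribution.
- If the 5% MRI loss is also applied, 105.6 infants remain and the difference is 8.18 (8.26 with t).

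The stated 8.1 lies within this range. It is compatible with the budgeted attrition and leaves no visible room for further removals.

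**3. Power if removals come on top.** The 36-week number is 65 × 0.95 = 61.75 per arm. The planned difference is taken as the one detectable there with 80% power (t-test), 0.508 SD. The extra removal r is an assumption. n per arm = 61.75 × (1 − r).

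| r | n per arm | detectable difference (SD) | power at 0.508 SD |
|---|---|---|---|
| 0 | 61.75 | 0.508 | 80.0% |
| 5% | 58.7 | 0.522 | 77.9% |
| 10% | 55.6 | 0.536 | 75.7% |
| 15% | 52.5 | 0.552 | 73.2% |

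For the Bayley at 2 years (8.1 points, SD 15), power goes from 0.812 to 0.792, 0.771 and 0.747 over the same values of r.

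**4. Bias if only retained infants are compared.** Let removed infants score D lower than retained infants, with removal rates r₁ and r₂. Leaving them out raises each arm's mean by D × r, so the bias is D × (r₁ − r₂), in favour of the arm that loses more. The error rate is the two-sided rejection probability under no true effect, at the 36-week numbers with removed infants taken out. All rates and deficits are assumed.

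| removal by arm | D | bias | two-sided error |
|---|---|---|---|
| equal | equal in both arms | 0 | 5.0% |
| 8% vs 4% | 5 points (SD 15) | 0.2 points = 0.01 SD | 5.1% |
| 10% vs 5% | 10 points (SD 15) | 0.5 points = 0.03 SD | 5.4% |
| 10% vs 5% | 1 SD | 0.05 SD | 5.8% |
| 15% vs 5% | 1 SD | 0.10 SD | 8.2% |

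In the last row, n is 61.75 × 0.95 = 58.7 and 61.75 × 0.85 = 52.5. The standard error is √(1/58.7 + 1/52.5) = 0.190 SD, so the bias is 0.10/0.190 = 0.53 standard errors.

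**The case against.** The strongest reply is that only the diet stops. The heading concerns the intervention, Intervention uses the term study period for the diet phase, and Informed consent has separate forms for the NICU and follow-up phases. That reading is available, so a total loss of outcomes is not established. But the sentence itself says otherwise and nothing in the article corrects it, so the need to reconcile the passages stands.

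A second reply is that missing-data detail belongs in the analysis plan. That is fair for the imputation model. It does not help with measurements that the protocol tells staff to stop taking.

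A third is that the numerical effect is small. For power this is right. For bias it depends on values the documents do not give, and it vanishes when removal and deficit are the same in both arms.

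Some stronger readings are tempting but not supported:
- A reader might count a later severe intraventricular haemorrhage as a trigger. The eligibility text limits that criterion to haemorrhage found before enrolment.
- A reader might treat all removals as additional to the 5%. Transfer and expected death overlap with it.
- A reader might take analysis of all enrolled infants to include infants who never had an arm. The Abstract and Sample size use the enrolled 130 as 65 per group, so this is loose wording only.
- A reader might conclude that harm will be concealed. Nothing says that NEC goes unrecorded, and the documents do not state that the added protein or fat causes gastrointestinal disease.

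Removal at parent request is ordinary withdrawal and no part of the defect.

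**Conclusion.** The conflict is real and rests on the article's own text: a post-randomisation removal rule stands beside an intention-to-treat promise, and the imputation sentence does not name removal by rule. Taken literally, the rule discards obtainable outcomes in infants with a poorer prognosis.

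The consequences are conditional. They require that follow-up actually stops; the bias calculated above also requires that removal rates differ by arm. Power falls by roughly 2 to 7 percentage points for 5–15% extra removal, which is modest. For a 5–10 point difference in removal and a 1 SD deficit, the bias is 0.05–0.10 SD, about 10–20% of the detectable 0.508 SD (0.05/0.508 and 0.10/0.508), and the error is 5.8–8.2%. Milder assumptions bring the error close to 5%. The main reason to act is the loss of the intention-to-treat estimate, with power second.

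**What to change.** Reconcile the discontinuation section with Statistical methods by separating stopping the study diet from leaving the study:
- Infants who meet a criterion after randomisation stay in follow-up, whatever is decided clinically about their diet.
- The already scheduled 36-week, MRI and 2-year assessments are done where feasible, unless consent is withdrawn.
- These infants are analysed in the assigned arm, among all randomised infants.
- Any data still missing for this reason are included in the multiple imputation.
- NEC and the other listed events are reported by arm.

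No rule on feeding or stopping the diet is proposed here.

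The cost is a short protocol change and a few more infants to follow at visits already scheduled. Some will not complete every assessment: infants who die or are transferred may be unavailable, and air displacement plethysmography needs the infant off respiratory support.
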